#### Secondary Outcomes

The secondary outcomes are as follows:

Length of hospital stays during the 12-month follow-up period, in terms of days and nights, will be collected. The number of consultations with a general practitioner, a medical specialist, or paramedical professional will be reported on the case report forms (CRFs). This information will mainly be collected during interviews with the foster caregiver using the RUD-Lite scale (Resource Utilization in Dementia questionnaire) [17]. This scale assesses the use of health care resources by people with dementia. The foster caregiver will complete this questionnaire at baseline and at subsequent follow-up visits (T3, T6, T9, and T12).Global cost of hospitalization will be retrieved from the local PMSI databases.Vital status (alive or deceased) will be collected at T3, T6, T9, and T12.For the diagnosis of lower respiratory tract infections, at least two of the following symptoms must be present and a doctor must confirm the clinical evidence: (1) cough (starting or worsening), which may produce phlegm; (2) specific clinical signs during auscultation; (3) fever (≥38 °C); (4) chest pain; (5) rapid, shallow breathing (≥25 per minute); and (6) confusion or increased dependency [16].Geriatric syndromes [18] in participants will be assessed at T0, T6, and T12 as follows:Frailty will be assessed using Fried’s phenotype [19], that is, 5 predefined physical frailty criteria such as weight loss, slowness, low physical activity, weakness, and exhaustion. This will be analyzed as a dichotomous variable, that is, 1=frail and 0=not frail.The level of cognitive deterioration of the participants will be assessed using the Mini-Mental State Examination (MMSE) [20,21]. This 30-item scale assesses the severity of cognitive deterioration through items such as orientation, learning, attention, arithmetic, memory, language, and constructive praxis. The scale is rated from 0 to 30, reflecting the level of cognitive impairment.Depression will be assessed using the Center for Epidemiologic Studies—Depression Scale (CES-D) [22] validated in French by Fuhrer and Rouillon [23]. This 20-item questionnaire assesses depressive symptomatology, including 4 positive polarity items (happiness, self-worth, confidence, and enjoyment). The frequency of symptom occurrence during the past week is assessed by the participant using a 4-point Likert scale (never, occasionally, quite often, and frequently). The score ranges from 0 to 60. The higher the score, the more significant the symptomatology. High depressive symptomatology corresponds to a score above 16. Data will be collected at baseline, T6, and T12. For statistical analyses, the variable will be dichotomized (1=presence of depression and 0=absence of depression).The total number of medications taken by participants will be collected directly from the RUD-Lite questionnaire, at T0, T3, T6, T9, and T12, to assess polypharmacy.The total number of falls since the last visit will be collected at each follow-up from the foster caregivers.The Short Physical Performance Battery [24,25] will help to assess sarcopenia. Three subtests measure lower-extremity functions: keeping balance (feet side-by-side, semitandem, tandem balance position, to be kept for 10 s each); walking 4 m at usual pace, yielding a gait speed ratio (meter per second); standing up and sitting down 5 times as quickly as possible with the arms folded. Each movement is scored 0-4 points out of a total score from 0 to 12, with higher scores showing better physical performance. If the total score is below 8, there is a risk of sarcopenia. For the analyses, the variable will be dichotomized accordingly (1=sarcopenia; 0=no sarcopenia).Undernutrition will be assessed with the short version of the Mini Nutritional Assessment [26]. This questionnaire assesses nutritional status. A score below 12 indicates probable undernutrition. For the analyses, the variable will be dichotomized accordingly (1=undernutrition; 0=no undernutrition).Sensory impairments (audition and vision) will be collected by directly asking the foster caregiver. Variables will be dichotomized accordingly (1=hearing/vision impairment; 0=hearing/vision impairment).The level of independence in ADL and incontinence will be assessed using the Katz scale [27], a 6-item scale assessing independence in 6 basic ADLs: bathing, toileting, transferring, eating, dressing, and incontinence. For each activity, a score of 1 indicates complete autonomy, a score of 0.5 indicates partial autonomy, and a score of 0 indicates complete dependency.The level of independence in IADL will be assessed using the Lawton IADL scale [28]. The Lawton IADL scale measures 8 items: using the telephone, shopping, preparing food, housekeeping, doing laundry, using transportation, handling medications, and handling finances. The score is from 0 to 8; a score of 8 indicates total autonomy, and 0 indicates total dependency. In France, the Autonomy, Gerontology Iso-Resources (AGGIR) questionnaire has been developed by public authorities to quickly assess the degree of dependency of elderly people and assign a dependency group, ranging from 0 (bedridden, completely dependent) to 6 (no help required, the person is autonomous in everyday activities).Psychological and behavioral symptoms in dementia will be assessed with the short version of the NeuroPsychiatric Inventory or NPI [29,30]. This scale assesses the psychological, behavioral manifestations (agitation, hallucinations, apathy, etc), neurovegetative symptoms (sleep and appetite), and the impact on the professional’s workload.Feeling of loneliness will be captured with the 14th item of the CES-D [22,23]: I felt lonely. The answer possibilities are never, occasionally, often, and frequently. The answer “often” or “frequently” indicates a feeling of loneliness.Risk of developing pressure ulcers will be assessed with the Braden scale, and pressure ulcers will be classified according to the National Pressure Ulcer Advisory Panel, European Pressure Ulcer Advisory Panel, and Pan Pacific Pressure Injury Alliance [31].Quality of life and adaptation will be assessed as follows:Quality of life of the participant will be assessed at baseline, T6, and T12 using the Questionnaire Quality of Life—Alzheimer’s Disease (QoL-AD) [32,33]. This 13-item questionnaire assesses the participant’s physical condition, mood, relationships with friends and family, financial difficulties, and overall quality of life. The questionnaire is to be administered to both seniors and caregivers, and thus is based on both self-rated health problems and proxy ratings from foster families. The items are evaluated using a 4-point ordinal scale ranging from poor to excellent, with a total score ranging from 13 to 52. For the weighted score, the participant’s score is multiplied by 2, the caregiver’s score is added, and the total is divided by 3 to bring the score back to the initial scale. In the proxy version, the foster caregiver will be asked to try to give the answer they think the participant would give.Health-related quality of life of the participant will be assessed with the EQ-5D questionnaire [34]. This questionnaire assesses health conditions. It is the most widely used questionnaire in medicoeconomic analyses. It allows health outcomes to be assessed in terms of quality-adjusted life-years (QALYs). This indicator summarizes the length and quality of life in a single figure. The result of a cost-utility analysis is expressed in terms of the cost of gaining one QALY (ie, 1 year lived in perfect health). To estimate QALY, health-related quality of life is designed on a continuum from 0 (death) to 1 (perfect health). Each health status is thus assigned a weight of 0 to 1; the higher the score, the higher the corresponding quality of life.On the first page, the participant has to indicate, for each of the 5 dimensions assessed (mobility, independence, routine activities, pain or discomfort, and anxiety or depression), the state in which he or she finds himself or herself, by choosing 1 of the 3 options with increasing severity: no problems, problems, and extreme problems. The answers can be combined to describe the residents’ health status, using a 5-digit number corresponding to the 5 answers.On the second page, the participant assesses his or her overall health using a standard vertical 20 cm visual analog scale (EuroQol visual analog scale), graduated from 0 to 100, from “best imaginable state of health” to “worst imaginable state of health.”The score will be collected at T0, T6, and T12. The interviewer will use both the participant version and the proxy version. In the proxy version, the foster caregiver will be asked to try to give the answer they think the participant would give.Adaptation to the nursing home setting will be assessed at baseline, T6, and T12 using the Castonguay and Ferron scale [35]. This is a 17-item scale designed to identify who do not experience a favorable adaptation to the living conditions in nursing homes. The participants answer yes or no to a series of statements about their daily life and habits in the residence. A score of 16 or 17 indicates a good general adaptation to life in the residence, whereas a score of 11 or less indicates significant difficulties.Foster caregivers’ quality of life will be assessed with the Medical Outcomes Study Short-Form General Health Survey—36 items (SF-36) [36], a widely validated health-related quality of life questionnaire that uses questions on physical, social, and psychological domains.Symptoms of burnout will be assessed with the Professional Quality of Life (Pro-QoL) scale [37]. This 30-item questionnaire yields 3 domain-specific scores: compassion fatigue (ie, the pleasure of being able to do your job well), work satisfaction, and burnout in helping professionals.

Table 2 shows an overview of data collection at each follow-up.

**Table 2 table2:** Data collection over time in the KASAF^a^.

			Baseline (T0)		Phone interview (T3 months)		Follow-up (T6 months)		Phone interview (T9 months)		Final visit (T12 months)
**Older residents—self-rated questionnaires and anthropometric measures**											
	CES-D scale^b^	X^c^				X				X	
	QoL-AD scale^d^	X				X				X	
	EQ-5D-3L scale^e^	X				X				X	
	Adaptation to the institution scale	X				X				X	
	MMSE score^f^	X				X				X	
	SPPB scale^g^	X				X				X	
	CDR score^h^	X				X				X	
**Foster caregivers—proxy-rated questionnaires about the resident**											
	Medical characteristics	X				X				X	
	Prescribed drugs	X				X				X	
	NPUAP-EPUAP^i^ score^i^	X				X				X	
	Braden scale	X				X				X	
	ADL^j^ and IADL^k^ scales	X				X				X	
	AGGIR score^l^	X				X				X	
	MNA-SF scale^m^	X				X				X	
	NPI-ES scale^n^	X				X				X	
	QoL-AD scale	X				X				X	
	EQ-5D-3L score	X				X				X	
	RUD-Lite scale^o^	X		X		X		X		X	
	Health events			X		X		X		X	
	Alive/dead status			X		X		X		X	
**Foster caregivers—self-rated questionnaires**											
	Sociodemographic characteristics	X				X				X	
	Pro-QoL scale^p^	X				X				X	
	SF-36 scale^q^	X				X				X	

^a^KASAF: Karukera Study of Ageing in Foster Families.

^b^CES-D: Center for Epidemiologic Studies—Depression Scale.

^c^X: information that will be collected during the indicative period.

^d^QoL-AD: Questionnaire Quality of Life—Alzheimer’s Disease.

^e^EQ-5D-3L: EQ-5D three-level version.

^f^MMSE: Mini-Mental State Examination.

^g^SPPB: Short Physical Performance Battery.

^h^CDR: Clinical Dementia Rating.

^i^NPUAP-EPUAP: National Pressure Ulcer Advisory Panel–European Pressure Ulcer Advisory Panel.

^j^ADL: Activities of Daily Living.

^k^IADL: Instrumental Activities of Daily Living.

^l^AGGIR: Autonomy, Gerontology Group Iso-Ressources.

^m^MNA-SF: Mini Nutritional Assessment Short-Form.

^n^NPI-ES, NeuroPsychiatric Inventory for Health Staff.

^o^RUD-Lite: Resource Utilization in Dementia—Lite Version.

^p^Pro-QoL: Professional Quality of Life.

^q^SF-36: Short-Form General Health Survey—36 items.

#### Expected Timeline

The first participant was included on November 16, 2020. The 1-year follow-up was ended in June 2022 (Table 1).

### Patient and Public Involvement

There was no patient or public involvement in the design and conduct of this study. Nevertheless, we have had discussions with associations of foster caregivers who would like to use our results to strengthen their professional training.

### Data Analysis

First, the analysis will describe the number of included participants, the inclusion curve (evolution of the number of people included between the first and last inclusion), the number of theoretical visits, the number of visits actually made, and the ratio of both (number of visits made or number of theoretical visits).

A description of the rate and causes of death and study dropout will also be provided.

The following quantitative variables described in terms of number of staff, mean, and interindividual SD and 95% CI of the mean, median, range, and IQR values: number of hospitalizations, total length of hospitalization, total cost related to hospitalizations, total number of consultations with a general practitioner, total cost of low respiratory infections, total number of falls, MMSE score, total number of drugs, NPI score, QoL-AD score, SF-36 score, and Pro-QoL score.

Qualitative variables (ordinal: AGGIR grid, feeling of loneliness; dichotomous: vital status; presence or absence: frailty syndrome, depression, undernutrition, visual impairment, hearing impairment, incontinence, ADL dependency, IADL dependence) of participants at inclusion will be described in terms of frequency and number.

Comparisons between the 3 times (T0, T6, and T12) will be performed using repeated-measures ANOVA for quantitative variables and the Cochran-Armitage test for trend for qualitative variables.

Statistical analyses will be performed using the RStudio software (version 2.7; Posit Software).

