## Abstract

**Background:**

With aging of the population, the search for alternative models of care adapted to older people with dependency is necessary. In this setting, foster families (1-3 older people per family) could be an alternative to nursing homes, residential care facilities, or community- and home-based care.

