Despite strong family support, living at home is sometimes difficult or impossible for seniors and their caregivers [3] (heavy dependency, exhaustion of caregivers, regular decompensation of chronic pathologies, etc). Moreover, social isolation, social vulnerability, and loneliness among older people living at home [4,5] increase the risk of adverse health events, notably mortality [6]. The most developed and successful model for dependent persons in high- and middle-income countries is the nursing homes. However, the transition from one’s home to a nursing home usually disrupts residents’ social life and lifestyle, and institutionalized older people experience a steeper cognitive decline than community-dwelling people [7], as well as a drop in quality of life [8] and an increase in psychotropic drug use [9]. For these reasons, we need to study alternative and transitional care models between home care and nursing home care, such as foster families. Because fostered older people (while still moving out of their own homes) are taken care of within a family context instead of a nursing home or other collective settings, foster care placement processes could be an alternative to institutionalization. This model has developed to a greater extent over the last few years in Guadeloupe. Nearly 200 foster families care for about 300 dependent older people, whereas there are 21 nursing homes for approximately 1500 residents. Foster caregivers, after getting official approval and attending a 20-hour training course, usually accommodate 1 to 3 people in exchange for a monthly fee. Their mission is to ensure the well-being of their residents and to enable them to maintain close social and family relationships. Other professionals may also provide additional nursing care if necessary. Little is known about the characteristics of foster caregivers and their residents. Two decades ago, a study from Cébula and Horel [10] showed that 61% of fostered older people were older than 80 years in France, and two-thirds were women. Every 6 of 10 older people lived at home or with their own family before entering foster care, and foster care was requested by the older person’s household in 63% of cases. Most foster caregivers were women (96%). Two-thirds of the foster caregivers were between 40 and 60 years old, and 16% of them were older than 60 years. Every 8 of 10 foster caregivers were “partnered people,” the majority of them being single-family home owners (95%). Nearly half of the foster caregivers were in a nonemployment situation (inactive, unemployed, integration, and training) before obtaining their foster caregiver license. The cost of foster family accommodation for seniors depends on the number of caregiving hours, because of the length and frequency of stay (in 94% of cases, it is a full time) and geographical location. The monthly fee includes rent, services rendered, a maintenance allowance, and a daily allowance. Monthly cost ranges from €1400 to €2100 (US $1521.98 to US $2282.97) per month [11].

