### Study Sample

A total of 250 residents will be recruited over 6 months among the 300 older residents currently in foster families. The primary end point will be the hospitalization rate at 12 months. A 30% hospital admission rate over a year has been reported in the Incidence of pNeumonia and related ConseqUences in nursing home Resident study in nursing home residents [16]. A change in the hospitalization rate from 30% to 15% would be considered as significant from a clinical and public health point of view. For an risk of 5% and 250 participants, the expected CI will be 4.4% for a hospitalization rate of 15% and 5.7% for a 30% rate.

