## Results

Recruitment opened in September 2020 and ended in May 2021, with 109 older people recruited and 56 respective foster caregivers. The 1-year follow-up was ended in June 2022. Data analyses are ongoing, and the first results are expected to be published in May 2023.

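### Residents are clustered within foster families, but the precision statement and the named analyses treat them as independent, so CIs on between-resident estimates are somewhat too narrow if co-residents are alike

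*Protocol article*

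**What the plan says.** All references are to the Protocol article.

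- **Clustering.** The Abstract describes "foster families (1-3 older people per family", and the Introduction says that caregivers "usually accommodate 1 to 3 people in exchange for a monthly fee". In the source population, "Nearly 200 foster families care for about 300 dependent older people". The Results section reports "109 older people recruited and 56 respective foster caregivers".
- **Shared rater.** Table 2 has a block of resident scales completed by the foster caregiver. It includes ADL and IADL, MNA-SF, NPI, Braden, RUD-Lite, and proxy QoL-AD and EQ-5D. Under Secondary Outcomes, falls come from the caregiver, and consultations come mainly from interviews with the caregiver.
- **Precision.** Study Sample states that, for 250 participants, "the expected CI will be 4.4% for a hospitalization rate of 15" percent, and 5.7% for a rate of 30%.
- **Analysis.** For the quantitative variables, Data Analysis plans "mean, and interindividual SD and 95% CI of the mean, median, range, and IQR values". Comparisons over T0, T6 and T12 use repeated-measures ANOVA and the Cochran-Armitage trend test. No section mentions a family effect, an ICC, a design effect, a mixed model or cluster-robust variance.

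**The concern.** Residents of one family share a home, a caregiver and, for many scales, a rater. If their values are positively correlated, 109 residents carry less information than 109 independent people, and a CI built from the between-resident SD and the resident count is too short.

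The Discussion itself gives a reason to expect some correlation on the primary outcome. It argues that caregivers' close knowledge of their residents could reduce avoidable hospitalizations. If caregivers differ in this respect, residents of the same caregiver will resemble each other in admissions, even though admissions are read from the hospital discharge database.

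At stake is the stated uncertainty of the hospitalization rate and, more so, of the caregiver-reported measures. These figures are meant for comparison with a twin study in nursing homes. Recruitment of 109 against a planned 250 leaves less precision to overstate.

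**Working it through.** **Inputs from the article.** Planned N = 250; rates of 15% and 30%; stated half-widths of 4.4% and 5.7% (Study Sample). Achieved: 109 residents and 56 caregivers (Results). Family size 1 to 3 (Abstract, Introduction). I treat one caregiver as one family. **Assumed:** the ICC, which the article does not give.

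**Step 1: reproduce the stated precision.** Half-width = 1.96 × √(p(1 − p)/n), residents independent.

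- p = 0.15, n = 250: 1.96 × √(0.1275/250) = 4.43%
- p = 0.30, n = 250: 1.96 × √(0.21/250) = 5.68%

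Both round to the stated figures, so the design effect used was 1. At n = 109 the same formula gives 6.70% and 8.60%.

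**Step 2: design effect at the mean family size.** m = 109/56 = 1.95 and DE = 1 + (m − 1) × ICC. CI width is multiplied by √DE, and the same factor applies to a mean number of hospitalizations as to a proportion. Coverage of a nominal 95% CI = 2Φ(1.96/√DE) − 1.

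| ICC (assumed) | DE | CI should be wider by | Coverage | Half-width, N = 250 (15% / 30%) | Half-width, N = 109 (15% / 30%) | Effective N of 109 |
|---|---|---|---|---|---|---|
| 0.05 | 1.047 | 2% | 94.5% | 4.5% / 5.8% | 6.9% / 8.8% | 104 |
| 0.10 | 1.095 | 5% | 93.9% | 4.6% / 5.9% | 7.0% / 9.0% | 100 |
| 0.20 | 1.189 | 9% | 92.8% | 4.8% / 6.2% | 7.3% / 9.4% | 92 |
| 0.30 | 1.284 | 13% | 91.6% | 5.0% / 6.4% | 7.6% / 9.8% | 85 |

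**Step 3: unequal family sizes.** With unequal sizes, m is replaced by Σm²/Σm. The article gives no size distribution, so I take three mixes that each yield 109 residents in 56 families, at ICC 0.3:

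| Families of size 1 / 2 / 3 | Σm²/Σm | DE | Correct SE larger by | Coverage |
|---|---|---|---|---|
| 3 / 53 / 0 | 215/109 = 1.97 | 1.29 | 14% | 91.5% |
| 19 / 21 / 16 | 247/109 = 2.27 | 1.38 | 17% | 90.5% |
| 29 / 1 / 26 | 267/109 = 2.45 | 1.43 | 20% | 89.8% |

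Together with the simple-mean figure of 13%, the range at ICC 0.3 is 13% to 20%. Under the most uneven mix, the widening at ICC 0.05 to 0.20 would be about 4% to 14% (√1.072 = 1.04; √1.290 = 1.14) instead of 2% to 9%.

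**Step 4: which outcomes.** Hospitalizations come from the discharge database, with the caregiver only confirming, so no shared-rater effect acts on them and the lower ICC range is the likelier one. NPI, falls and consultations come from the caregiver and are among the variables given a CI in Data Analysis, so the higher value is more plausible there.

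**The case against.** **The article prints no CI formula.** A between-resident SD is a descriptive statistic, and the choice of variance estimator may sit in a fuller document. This stands for Data Analysis, where independence is read from the named methods. It does not stand for Study Sample, where independence is shown by reproduction.

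**The effect on the primary outcome is small.** At ICC 0.05 to 0.10, 4.4% becomes 4.5% to 4.6%, and 5.7% becomes 5.8% to 5.9%. This stands, and it limits the weight of the point.

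**A finite-population correction works the other way.** Recruitment is from about 300 current residents. For inference to them alone, the SE factor is √((300 − 109)/299) = 0.80 at N = 109 and √(50/299) = 0.41 at N = 250, so the stated half-widths would be too wide. This is correct for that target. The Conclusions and Discussion, however, plan comparison with nursing homes and possibly other settings, which asks about the care model beyond the present residents.

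**The planned tests compare time points within residents.** A stable family or rater effect largely cancels in such contrasts, whereas a change shared within a family does not. A reader might infer that every test is too liberal, but the direction of error is not established.

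**Two stronger readings lack support.**

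- Because "NPI score, QoL-AD score, SF-36 score, and Pro-QoL score" stand in one list, a reader might infer that the caregiver scales would be counted once per resident. Secondary Outcomes and Table 2 assign SF-36 and Pro-QoL to the caregivers under their own heading, the 56 caregivers are counted separately, and nothing describes a resident-level file for them.
- A reader might also infer that the caregiver decides when a resident seeks care. No section says so.

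**Conclusion.** The point holds at modest size. The stated precision assumes independent residents and the named analyses carry no family term, in a sample averaging 1.95 residents per caregiver. CIs on between-resident estimates are too narrow under two conditions: within-family correlation is positive, and inference reaches beyond the roughly 300 current residents.

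For the hospitalization rate, the shortfall is about 2% to 9% of CI width at an assumed ICC of 0.05 to 0.20 and mean family size. For caregiver-reported measures at an assumed ICC of 0.3, correct SEs are about 13% to 20% larger (equivalently, unadjusted SEs are about 12% to 17% too small), with coverage of about 90% to 92%. These sizes rest on the assumed ICC and on the family-size mix, neither of which the article gives. Point estimates are not at issue.

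**What to change.** 1. Compute resident-level CIs with variance clustered on the foster family (sandwich estimator) or from a model with a random family intercept.
2. Include the family in the models for the T0, T6 and T12 comparisons, so that the result does not depend on which way the error would go.
3. Restate the expected precision with a design effect over a stated ICC range such as 0.05 to 0.30, using the actual family-size distribution, and say that the target of inference extends beyond the current residents.
4. Report the estimated ICC for the main outcomes, which the comparison with the nursing-home study can use.

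No new data are needed beyond the link between each resident and the caregiver. The cost is somewhat wider CIs.

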To date, we do not know whether foster care is an alternative to nursing home care, as suggested by the limited existing literature, or a transitional care setting between home care and nursing home care. Epidemiological and medicoeconomic data on older people in foster families are essential to assess the relevance of this type of care, in particular, according to the severity of dementia or the degree of dependence in ADLs. Several issues need to be clarified: what is the residents’ annual hospitalization rate and the associated costs? What is the health care pathway of residents in terms of consultations with general practitioners, specialists, and paramedics? What is the prevalence of geriatric syndromes in this population, and the incidence of mortality? What is the incidence of pneumonia, the leading cause of death and emergency hospitalization in older people? What is the quality of life of the residents and their foster caregivers? The Karukera Study of Ageing in Foster Families (KASAF) is a prospective cohort study, designed to investigate these questions. This longitudinal study will assess the health status and medical and economic data of 250 foster family residents and their foster caregivers over a year.

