### Objectives

This study is an epidemiological study that aims to explore the characteristics of foster family residents and caregivers. We have identified a number of outcomes that may provide insight on their profile. As hospitalization is the main expensive item in the health trajectories of older people [16], the primary objective of the KASAF is to study hospital admission rates of residents of foster families over a year.

Several secondary objectives are also targeted: length of hospital stays during the 12-month follow-up period; number of consultations with a general practitioner, a medical specialist, or a paramedical professional; global cost of hospital stays; prevalence of geriatric syndromes (frailty, undernutrition, depressive symptoms, incontinence and dependency, sensory impairments; falls; polypharmacy; bedsores; and cognitive impairment); incidence of lower respiratory tract infection; quality of life of foster care recipients and their foster caregivers; and burnout in foster caregivers.

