Foster families have never been formally assessed, the most robust results dating back to 30 years. In theory, it is less expensive than nursing homes for the community, but in the absence of scientific studies on the associated health outcomes (number of hospitalizations, deaths, etc), this model has not been validated and remains rare in metropolitan France. Yet, foster caregivers could be valuable assets in health care, thanks to their intimate knowledge of older persons and their pathologies, compared with nursing home staff, which have a high turnover, thus reducing avoidable hospitalizations and medical consultations.

Moreover, in the event of a health crisis such as the one experienced with the COVID-19 pandemic, measures of isolation and social distancing are much easier to implement, as foster family residents live in small family units, usually have single rooms, with less comings and goings than in nursing homes. The collected data will be used for exploring the characteristics of the foster home residents with aims that might not be considered today (1) because they are out of topic and (2) because science evolves.

This study presents limitations. We will not have access to data from informal caregivers, who could provide different insights on the participant’s state of mind or daily life. Also, cost analyses will focus only on hospitalization costs. This is why an ancillary study will be carried out after the end of the KASAF, using information from the national health insurance database. This study will accurately assess the cost of the entire health care pathway, including nursing, medical transportation, and other health care expenses. Finally, the KASAF does not include randomized interventions versus nursing home limiting causal interpretations of the results.

We hope that our results will help introduce more rationality into social and economic debates, sometimes led by accounts of personal experiences and extrapolated indicators, often for lack of robust data, and help ensure that public health policies are based on sound scientific evidence. Indeed, our data will be used to support the coordination of institutional funding bodies, especially resource allocation.

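### The analysis list names a cost of lower respiratory infections where the stated objective is their incidence

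*Protocol article*

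**What the plan says.** **Lower respiratory infection.** The Introduction asks "What is the incidence of pneumonia, the leading cause of death and emergency hospitalization in older people". The Objectives section carries this over into the secondary objectives, which end with "incidence of lower respiratory tract infection; quality of life of foster care recipients and their foster caregivers; and burnout in foster caregivers". Secondary Outcomes gives the case definition, which begins "For the diagnosis of lower respiratory tract infections, at least two of the following symptoms must be present" and also requires confirmation by a doctor. In Data Analysis, the list of quantitative variables has one item on these infections: "total cost of low respiratory infections". The list of qualitative variables has none.

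**Costs.** Secondary Outcomes names one cost and its source: "Global cost of hospitalization will be retrieved from the local PMSI databases". Among the limitations, the Discussion says that "cost analyses will focus only on hospitalization costs".

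**Pro-QoL.** Secondary Outcomes says the questionnaire gives three domain scores, described as "compassion fatigue (ie, the pleasure of being able to do your job well), work satisfaction, and burnout in helping professionals". The quantitative list in Data Analysis ends with "SF-36 score, and Pro-QoL score".

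**The concern.** An incidence and a cost answer different questions. The article asks how often these infections occur, defines how to recognise one, and then lists for analysis only what they cost. A cost restricted to hospital stays also depends on who is admitted. That decision may differ between foster families and the nursing homes of the planned twin study, with which the Discussion hopes to compare all variables of interest. A comparison of LRTI cost could then reflect admission practice and not the frequency of infection.

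The Pro-QoL wording raises a smaller question. Caregiver burnout is an objective, but the analysis list does not name a burnout score. The outcome text also explains compassion fatigue by a phrase that describes its opposite. Someone labelling the domain scores from this text could get the direction of one of them wrong.

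**Working it through.** The article gives no figure for LRTI or Pro-QoL, so there is none to reproduce on this point. Its only design figures are the CI half-widths for the hospitalization rate with 250 participants. They follow from 1.96 × √(p(1 − p)/n):

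- p = 0.15: 1.96 × √(0.15 × 0.85/250) = 4.43%, stated as 4.4%.
- p = 0.30: 1.96 × √(0.30 × 0.70/250) = 5.68%, stated as 5.7%.

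Both agree, and neither is touched by this point. The rest is a comparison of text.

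**Step 1: LRTI through the article.**

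| Section | Quantity |
|---|---|
| Introduction | incidence of pneumonia |
| Objectives | incidence of LRTI |
| Secondary Outcomes | a doctor-confirmed clinical event; no LRTI cost defined |
| Data Analysis, quantitative list | total cost |
| Data Analysis, qualitative list | no LRTI item |

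The first three rows agree with one another. The analysis list departs from them.

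**Step 2: can the listed cost stand in for incidence?** With hospital costs only, the mean LRTI cost per resident is

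mean cost = (episodes per resident) × (fraction of episodes admitted) × (mean hospital cost per admitted episode).

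One number cannot be solved for three unknowns. If episodes per resident double and the fraction admitted halves, then 2 × ½ = 1 and the mean cost is unchanged, although incidence has doubled. The article gives no admitted fraction, so the gap cannot be sized. It disappears only if every episode leads to admission and the cost per admission is known.

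**Step 3: Pro-QoL.** Secondary Outcomes gives three domain scores and no other scoring. Data Analysis uses a singular and does not say which domain, or whether all three, will be described. No text speaks of an overall, total or summed score. The SF-36, which Secondary Outcomes describes as covering several domains, appears in the same list in the same singular form.

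**Step 4: the compassion fatigue explanation.** Taking pleasure in doing one's work well is satisfaction, not fatigue. Satisfaction is the next domain in the same sentence. The explanation is attached to the wrong term.

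**The case against.** The strongest defence is that the cost item is a slip and the list is a condensation. The consultation, fall and drug items in the same list are all counts, so a count was probably meant here too. The list is plainly not exhaustive: it also omits the EQ-5D, the physical performance battery, pressure ulcers, the adaptation scale, and specialist and paramedical consultations. Table 2 schedules health events at 3, 6, 9 and 12 months, and the objective and case definition remain in place.

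Much of this stands. A reader might infer that the study will report no LRTI incidence at all; an incomplete list does not establish that. The defence does not remove the error, however. LRTI is not simply left out of the list. It is there with a different quantity, and that is a wrong statement whether or not it is a slip.

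A reader might also infer that the cost cannot be obtained. That goes too far: the cost of LRTI admissions could come from the hospital discharge database. What the plan cannot supply is a cost covering episodes treated outside hospital. The Discussion discloses this limit and defers the cost of the whole care pathway to an ancillary study.

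Finally, a reader might infer that the three Pro-QoL domains will be added into one score, so that falling satisfaction masks rising burnout. No section proposes such an addition, and the SF-36 item suggests that the list uses instrument names as shorthand. That stronger reading is not supported.

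**Conclusion.** The point holds for LRTI. The analysis list names a cost that is neither an objective nor a defined outcome, in place of the incidence that the article asks for and defines. One secondary objective is affected. The primary outcome, the sample size and the precision statement are not. The numerical effect cannot be estimated, because the article gives neither an LRTI frequency nor the share of episodes admitted.

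The two Pro-QoL matters are wording corrections only. The singular is ambiguous, and burnout has a defined domain score even though the analysis list does not name it. The misplaced explanation of compassion fatigue is a clear slip, but it changes no calculation.

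The conclusion rests on reading the list as written. If the full protocol or analysis plan, which is not shown, lists an LRTI count, only the article's sentence needs correcting.

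**What to change.** 1. In Data Analysis, replace the LRTI cost item with the number of LRTI episodes and their incidence with a 95% CI. Either a rate over person-time or the proportion of residents with at least one episode would answer the objective. State which one; a rate over person-time allows for residents who die or leave before 12 months.
2. If a cost is wanted, keep it as an optional item labelled as the hospital cost of LRTI admissions.
3. In the same list, name the three Pro-QoL domain scores and identify burnout as the one that answers the caregiver objective.
4. In Secondary Outcomes, move the explanation about pleasure in the work from compassion fatigue to the satisfaction domain.

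These are wording changes with no effect on sample size. They need no new data, provided that the health events recorded at follow-up include LRTI episodes that meet the case definition. The article implies this but does not say so, and it should be confirmed against the case report form.
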